#### MV indication

The infant will receive MV therapy if any of the following condition occurs: (1) FiO_2_ ≧ 0.45, PEEP > 8 cmH_2_O, SPO_2_ < 90%, and the condition lasts > 15 min; (2) frequent or severe apnea even after the caffeine therapy. In the trial, ≥ four episodes of apnea requiring vigorous stimulation in 6 h is defined as frequent apnea, and severe apnea defined as ≥ 2 episodes requiring positive pressure ventilation in 6 h; (3) persistent (confirmed by two arterial blood gas samples at least 30 min apart) respiratory acidosis with pH < 7.20 and PCO_2_ > 65 mmHg; (4) critical circumstances requiring intubation such as cardiac arrest caused by severe metabolic acidosis [8]. These criteria only apply to infants aged ≤ 1 week, and will be used only for the first time after birth to judge whether MV management should be conducted instead of noninvasive ventilation.

#### Indication for the weaning from MV

The infant will be weaned from MV if all the following criteria are achieved. All preterm infants in this trial will receive caffeine therapy at least 24 h before weaning. Caffeine therapy with a loading dose of 20 mg/kg and then a maintenance dose of 5–10 mg/kg is encouraged in the trial. These criteria are as follows:
The arterial blood gas should be maintained in a targeted range (pH ≧ 7.20, PaO_2_ ≧ 50 mmHg, PaCO_2_ ≦ 60 mmHg) with a low positive pressure (mean arterial pressure (MAP) ≦ 7 cmH_2_O, FiO_2_ ≦ 0.3).Stable spontaneous breathing should be present.

#### Indication for noninvasive support weaning

The infant will be weaned from NCPAP or NIPPV, if it has been 24 h since all of the following criteria will be achieved:
MAP/PEEP ≦ 3–5 cmH_2_OFiO_2_ ≦ 0.25No apnea and bradycardia that requires stimulation

#### Termination of the study

Death in hospitalizationEarly dropout on account of parents’ decision

### Outcomes

#### Primary outcomes

The primary outcomes will be as follows:
Mortality, co-morbidity, and severity of BPD at 36 weeks of corrected gestational age.MV requirement in the first 72 h of life.

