**Methods:**

The **L**ISA **O**r **L**ow **P**eak **P**ressure trial is to be conducted in 14 tertiary neonatal intensive care units in China. A total of 600 preterm infants born with gestational age between 25^0/7^ and 31^6/7^ weeks and with a primary diagnosis of RDS will be involved in the study. Infants will be randomized to the LISA or LPPSA group when surfactant therapy is indicated. Primary outcomes include mortality, severity of bronchopulmonary dysplasia at 36 weeks of postmenstrual age (PMA), and mechanical ventilation (MV) in the first 72 h of life. Secondary outcomes include the days of MV, duration of all sorts of non-invasive respiratory support, fraction of inspired oxygen, oxygen saturation before and after surfactant administration, and time required to perform the procedure for surfactant administration. The incidence of comorbidities, including retinopathy of prematurity (ROP), necrotizing enterocolitis (NEC), intraventricular hemorrhage (IVH), hemodynamically significant patent ductus arteriosus (hsPDA), pneumothorax, and massive pulmonary hemorrhage within 48 h of surfactant administration, and the failure rates of each technique will be determined.

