## Background

In the last several years, dramatic improvements have been made in the management of respiratory distress syndrome (RDS) in preterm infants, including early establishment of FRC by noninvasive respiratory support, early rescue instead of prophylactic surfactant use, and curtailed application of mechanical ventilation (MV). All these changes have greatly improved the outcome for babies with RDS [1, 2].

Less invasive surfactant administration (LISA), as an innovative mode of surfactant delivery, is getting increasing attention in the management of preterm infants with RDS. This technique is characterized by the use of a thin catheter to deliver surfactant instead of an endotracheal tube and by keeping continuous positive airway pressure (CPAP) support during the course of administration [3]. A recent systemic review and meta-analysis in preterm infants with RDS indicated that surfactant administration via the LISA method decreased the combination rate of mortality or bronchopulmonary dysplasia (BPD) and reduced need for MV during the first 72 h of life [4]. However, the implementation of the technique requires an experienced clinician and consistence when performing the procedure. Moreover, the mechanisms underlying the beneficial effect of LISA over conventional methods are not fully understood, and further research is warranted [5]. While the intubation-surfactant-extubation (INSURE) technique as a conventional method has been widely used, evidence on superiority, efficacy, and safety of the LISA method over conventional surfactant administration are needed.

To provide more evidences and elucidate the potential protective mechanisms of the LISA method, we therefore conduct a multicenter, prospective, randomized controlled trial in China. This trial aims to compare the effects of the LISA method with those of endotracheal surfactant administration immediately followed by positive pressure ventilation with a designated lower peak pressure than it does in INSURE (LPPSA) in preterm infants with RDS and indicated for surfactant administration. Our hypothesis is that the effects of designated low positive pressure ventilation use following conventional surfactant administration (LPPSA) are not inferior to LISA in the treatment of preterm infants with RDS.

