**Assessments**					
**Primary outcomes** 1.Need for ventilation during the first 72 hours				X	
2. Mortality 3. BPD					X
**Secondary outcomes** Need for and the duration of MV (days), duration (days) of non-invasive respiratory support, severe co-morbidities, pneumothorax, massive pulmonary hemorrhage within 48 h of surfactant administration, hemodynamically significant patent ductus arteriosus that needs medical or surgical intervention, Duration of hospitalization, Failure rate of LISA or LPPSA			X	X	X

*LPPSA* surfactant administration followed by low peak pressure, *LISA* less invasive surfactant administration

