### Statistical methods

All data will be analyzed using SPSS version 20.0. To compare primary and secondary outcomes between the two groups, Student’s t-test (continuous variables) and the chi-squared test (categorical variables) will be used. The two-level hierarchical linear regression model or the logistic regression model, whichever is appropriate, will be applied for the comparison of the outcomes between the two groups, accounting for the infants’ characteristics, such as gestational age, birthweight, sex, appropriateness for gestational age, delivery mode, and pregnancy complications, and center variables, such as number of beds in the NICU and the number of infants with gestational age < 32 weeks. *P* < 0.05 will be regarded as statistically significant.

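### The primary outcomes are listed inconsistently, no outcome or analysis is named as deciding at the flat 0.05 level, and BPD has no general rule for infants who die before it can be assessed

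*Protocol article*

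**What the plan says.** **Lists of primary outcomes (Protocol article).**
- Abstract, Methods: "Primary outcomes include mortality, severity of bronchopulmonary dysplasia at 36 weeks of postmenstrual age (PMA), and mechanical ventilation (MV) in the first 72 h".
- Study aim: mortality, incidence of BPD, and MV in the first 72 h.
- Primary outcomes: "Mortality, co-morbidity, and severity of BPD" at 36 weeks corrected age, then "MV requirement in the first 72 h of life".
- Table 1, Assessments: "Need for ventilation during the first 72 hours" as number 1, then "2. Mortality 3. BPD". Severe co-morbidities appear in the secondary row.

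**Sizing.** The sample size rests on the incidence of BPD alone.

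**Analysis.** Statistical methods applies a t-test or chi-squared test to primary and secondary outcomes, and also a two-level linear or logistic model adjusted for infant and centre variables. One threshold covers everything: P below "0.05 will be regarded as statistically significant".

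**Deaths.** Under Definitions, BPD needs at least 28 days of supplemental oxygen plus status at 36 weeks PMA or discharge home, whichever is first. Termination of the study lists death in hospital. The only rule for deaths is that an early death from lethal BPD is recorded separately.

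**Prior evidence.** The Background says that LISA "decreased the combination rate of mortality or bronchopulmonary dysplasia (BPD" and reduced the need for MV in the first 72 h.

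**The concern.** A confirmatory trial should let a reader say in advance which result decides it. Here co-morbidity is primary in one section and secondary in Table 1, and it is never defined as an endpoint. BPD could be a graded or a yes/no variable. Each outcome can yield two P values, one crude and one adjusted. With no order, alpha split or success rule, several results could each be presented as the primary finding.

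The second problem is death as a competing event. An infant who dies early cannot be classified as having BPD. Whether such infants are left out or scored as free of BPD, more deaths can mean less recorded BPD. This matters more because the Background hypothesis is that LPPSA is not inferior to LISA, and a distorted BPD rate could make a worse arm look acceptable.

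**Working it through.** **1. The lists side by side**

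| Section | Mortality | Co-morbidity | BPD | MV in 72 h |
|---|---|---|---|---|
| Abstract | primary | not primary | severity | primary |
| Study aim | yes | no | incidence | yes |
| Primary outcomes | primary | primary, undefined | severity | primary |
| Table 1 | primary | secondary (severe) | not specified | primary |
| Sample size | no | no | incidence | no |

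Two conflicts emerge: co-morbidity, and incidence against severity of BPD.

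**2. The plan's own figure.** It states 258 per group: 25% BPD, 20% reduction, alpha 0.05, power 0.8. With the two-sided two-proportion formula:
- Relative reduction, 25% vs 20%: 1094 per group. With 258, power is 27%.
- Absolute reduction, 25% vs 5%: 49 per group.
- Nearest variant, 25% vs 15%, which is not stated: 250 per group, or 270 with continuity correction.

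The 258 is not reproduced. It is relevant here because power for any new primary outcome depends on which effect is meant.

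**3. Family-wise error.** Assume that any one significant primary outcome counts as success and that each is tested at 0.05.
- Independent: 1 − 0.95^k. For k = 2, 1 − 0.9025 = 9.8%. For k = 3, 1 − 0.8574 = 14.3%.
- k = 3 with equally correlated normal test statistics (simulated, correlations assumed): 13.6% at 0.3, 12.5% at 0.5, 9.8% at 0.8.
- k = 4 would give 18.5% if independent, but this treats the undefined co-morbidity as exactly one test.

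**4. Deaths and BPD.** The article gives no mortality rate, so these rates are assumed. Let 30% of each arm have death or BPD, with deaths of 5% and 10%.
- BPD over all randomised, deaths scored as no BPD: 30 − 5 = 25% vs 30 − 10 = 20%.
- BPD among survivors: 0.25/0.95 = 26.3% vs 0.20/0.90 = 22.2%.
- Death or BPD: 30% in both.

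The arm with twice the deaths looks better on BPD under either convention. In a second case, let survivor BPD be 25% in both arms with the same deaths:
- BPD over all randomised: 0.95 × 0.25 = 23.8% vs 0.90 × 0.25 = 22.5%.
- Death or BPD: 5 + 23.75 = 28.8% vs 10 + 22.5 = 32.5%.

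Here scoring deaths as no BPD favours the arm with more deaths, while excluding them shows no difference.

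**5. Power for a composite (effects assumed; two-sided difference test).**
- 30% vs 24%, a 20% relative reduction: 34% power with 258 per group.
- 30% vs 20%, an assumed 10-point difference: 75% with 258 and 81% with 300 per group.

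**6. Cost of splitting alpha.** For 25% vs 15% (assumed) with 258 per group, power falls from 81% at 0.05 to 67% at 0.05/3 = 0.0167.

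**The case against.** - **The lists largely agree.** The abstract, Study aim and Table 1 name the same three endpoints. A reader might infer three conflicting lists, but the only extra item is co-morbidity in the Primary outcomes section. The other difference is severity against incidence of BPD. This objection stands.
- **The inflation is conditional.** A reader might take 14.3% or 18.5% as the trial's actual error rate. Those figures need independence and a rule that any one significant outcome suffices, and the protocol states no such rule. If all had to succeed, alpha would not inflate, but power would fall. Read alone, the Primary outcomes section has two items, which gives 9.8%. Against that reading, Table 1 numbers mortality and BPD separately and no composite is defined.
- **A SAP may settle it.** Testing order and the choice between crude and adjusted analysis are often left to a SAP, which is not shown. It could supply both. It could not reconcile the lists without overruling a section of this article.
- **Survivors only.** A reader might infer that BPD will be analysed only in survivors. No section fixes that denominator, and lethal-BPD deaths are addressed in part. What stands is that the article does not say how those deaths count, and it gives no rule for other deaths.
- **Mortality is itself primary.** Excess deaths would be reported beside BPD. Death or BPD can be derived from the data collected, and MV in 72 h is already primary, so it does not follow that the results could not be compared with earlier evidence.
- **Other remedies exist.** Split alpha also controls error, so a single composite is not the only acceptable design.

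**Conclusion.** The point holds in this form. Co-morbidity is primary in one section and secondary in Table 1 without being defined. BPD shifts between severity and incidence. One flat threshold covers crude and adjusted comparisons, with no deciding outcome or analysis named. If any one primary outcome sufficed, the false-positive rate for three would be at most 14.3% if they are independent, and about 10% to 14% under assumed correlations of 0.3 to 0.8.

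The distortion of BPD by early death follows from the definition itself. Its size and direction depend on mortality, which the article does not give, so the 26.3% vs 22.2% contrast illustrates the mechanism and does not forecast the result. The inconsistencies lie in the article's own text and should be resolved before any between-group analysis.

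**What to change.** 1. Remove co-morbidity from the primary list so that the abstract, Study aim, Primary outcomes and Table 1 agree. State whether BPD is analysed as incidence or grade.
2. Name one deciding primary outcome that counts deaths, for example death before, or BPD at, 36 weeks PMA in all randomised infants. State the BPD grade threshold and reconcile it with Definitions, which requires oxygen at 36 weeks yet grades infants in room air as mild.
3. Name one deciding analysis. The two-level model already planned, adjusted for gestational age, can serve, with the chi-squared test as supportive.
4. Control error across the remaining primaries by fixed sequence (MV in 72 h next) or split alpha. Report mortality and BPD as components.
5. Match the test to the hypothesis: non-inferiority with a stated margin, or superiority. A difference test at 0.05 does not address the non-inferiority hypothesis in the Background.
6. Restate the planning rate and power for the composite under an explicit effect.

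**Cost.** The change is to protocol and SAP wording; mortality, BPD and MV are already collected. MV in 72 h could be claimed only within the hierarchy or at a smaller alpha. The restated power may be less favourable: with 258 per group and a difference test, it ranges from 34% (30% vs 24%) to 75% (30% vs 20%), both assumed effects. A non-inferiority test would need its own calculation once a margin is set.

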#### Secondary outcomes

The secondary outcomes will be as follows:
Need for and duration of MV (days) during of hospitalizationDuration of noninvasive respiratory support (days)Duration of oxygen need.Heart rate and oxygen saturation before and after surfactant administration in every 30 s for 10 min.Incidence of pneumothorax and massive pulmonary hemorrhage within 48 h of surfactant administrationSevere neonatal diseases including and hemodynamically significant patent ductus arteriosus (hsPDA) that needs medical or surgical interventionDuration of hospitalizationFailure rate of operation (including LISA or LPPSA technique)Time required to perform the procedure of surfactant administration.

### Other data

Other infant information that will be collected is as follows: gestational age, birth weight, sex, delivery mode, Apgar score at 1 and 5 min, antenatal steroid use, prolonged premature rupture of membrane (> 18 h), intraventricular hemorrhage (IVH, grade 3–4), stage II-III necrotizing enterocolitis (NEC), retinopathy of prematurity (ROP, ≧ III stage), and postnatal steroid use.

### Definitions

#### BPD

BPD is defined as postnatal treatment with oxygen > 21% for at least 28 days, plus oxygen requirement at 36 weeks PMA [9]. According to our inclusive criteria, the time point of the assessment is 36 weeks PMA or discharge to home, whichever comes first, and the grading criteria are as follows: (1) mild, breathing room air; (2) moderate, need for < 30% oxygen; and (3) severe, need for ≥30% oxygen and/or positive pressure support [9]. If the infant dies in the early days of life because of lethal BPD, a special case will be recorded separately according to revised definition of BPD [10].

#### NEC (proven and advanced)

Proven NEC (stage II) encompasses the signs of stage I plus the absence of bowel sounds with or without abdominal tenderness. Abdominal tenderness is present, and some infants have cellulitis of the abdominal wall or a mass in the right lower quadrant. Infants with stage IIA are mildly ill, whereas those with stage IIB NEC are moderately ill and have mild metabolic acidosis and thrombocytopenia. Findings on abdominal imaging include intestinal dilation, ileus, ascites, and pneumatosis intestinalis, which is the defining feature of stage II.

Advanced NEC (stage III) is the most severe form. In stage IIIA, the bowel is intact, whereas stage IIIB is characterized by bowel perforation visualized as a pneumoperitoneum on the abdominal radiograph. Infants with advanced NEC are critically ill. In addition to the signs shown in the less severe stages, they typically have hypotension, bradycardia, severe apnea, and signs of peritonitis (abdominal distention and marked tenderness). Laboratory signs include a combined respiratory and metabolic acidosis, neutropenia, and disseminated intravascular coagulation [11].

#### IVH (grades III and IV)

IVH with grade III is defined as IVH involving more than 50% of the ventricular area; lateral ventricles are usually distended. IVH with grade IV is characterized by hemorrhagic infarction in the periventricular white matter ipsilateral to IVH [12].

#### Severe ROP

Severe ROP, defined as ROP needing surgical intervention, including intravitreal injection, laser therapy, and cryotherapy, will be recorded in our study [13].

#### Massive pulmonary hemorrhage

This condition is characterized by the presence of hemorrhagic fluid from the endotracheal tube, accompanied by a sudden respiratory distress and deterioration of clinical condition (increased parameters or MV therapy is required with 1 h of the occurrence of blood fluid). X-ray imaging suggests involvement of more than two lung lobes [14].

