### Grouping

Infants will be divided into two groups, namely, the LISA group or LPPSA group, according to the method of surfactant administration. Infants in the LISA group will receive surfactants by using a thin catheter (LISA catheter® designed by Shuanghe Pharmaceutical, Beijing). Infants will be on nasal continuous positive airway pressure (NCPAP) support during the course of surfactant administration. Infants in the LPPSA group will be given surfactant by traditional intubation and MV support with a T-piece or ventilator immediately following surfactant administration as done in INSURE but with a peak inspiratory pressure at < 15 cmH_2_O (12–15 cmH_2_O), positive end-expiratory pressure (PEEP) at 6–8 cmH_2_O, and respiratory rate at 40–60 breaths per minute.

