#### LPPSA method

The same principle of premedication will be applied. Surfactant will be administered through an endotracheal tube under direct vision by laryngoscopy. Surfactant will be continuously administered through an endotracheal tube with mechanical ventilator or T-piece resuscitator. The initial setting will be as follows: PEEP of 6–8 cmH_2_O, peak inspiratory pressure of 12–15 cmH_2_O, and respiratory rate of 40 breaths per minute. If the infant develops apnea, bradycardia, or desaturation, surfactant administration will be stopped immediately. If the condition does not improve in 30 s, then conventional peak pressure ventilation (18–20 cmH_2_O or more), will be given, and the case will be considered as a failure case of LPPSA.

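### Massive pulmonary hemorrhage is defined by blood from an endotracheal tube, which only LPPSA infants have by design; this permits a probably small under-count in LISA that a device-neutral wording would remove

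*Protocol article*

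**What the plan says.** All references are to the protocol article.

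- **Source of blood** (Definitions, Massive pulmonary hemorrhage): "This condition is characterized by the presence of hemorrhagic fluid from the endotracheal tube". No other source is named.
- **Deterioration** (same definition): sudden respiratory distress and clinical worsening must accompany the blood, specified as "increased parameters or MV therapy is required with 1 h of the occurrence of blood fluid".
- **Imaging** (same definition): "X-ray imaging suggests involvement of more than two lung lobes".
- **LISA arm** (Grouping): "Infants in the LISA group will receive surfactants by using a thin catheter", and "Infants will be on nasal continuous positive airway pressure (NCPAP) support during the course of surfactant administration".
- **LPPSA arm** (LPPSA method): "Surfactant will be administered through an endotracheal tube under direct vision by laryngoscopy". Grouping adds "MV support with a T-piece or ventilator immediately following surfactant administration as done in INSURE", and the Background spells out that model as the "intubation-surfactant-extubation (INSURE) technique as a conventional method". No extubation time is given for LPPSA.
- **Afterwards** (CPAP and NIPPV): NCPAP is the main noninvasive support during and after surfactant, with no distinction by arm.
- **Use of the outcome:** incidence within 48 h of surfactant is a secondary outcome. The condition is also a listed adverse event followed by the safety committee (Adverse events).

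**The concern.** The sign that opens the definition depends on a device, and that device is part of what separates the arms. Two infants with the same bleed, the same deterioration and the same X-ray can be classified differently because one has a tube and the other is on NCPAP. Blinding the outcome assessors does not help: if no tube was present, the record cannot show blood from one.

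The definition also fits poorly with itself. It has a branch for infants who come to need mechanical ventilation, yet its blood criterion cannot be met by an infant without a tube. The one-hour limit runs from the appearance of blood, and it is unclear whether blood at the mouth of an infant on NCPAP starts that clock.

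At stake is a comparison of harm between two techniques in a trial whose Background hypothesizes that LPPSA is not inferior to LISA. A device-linked under-count would fall more on LISA and make LPPSA look slightly worse. A larger sample would not remove it.

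**Working it through.** The plan gives no hemorrhage rate, power or sample size for this outcome, so there is no figure to reproduce. The check has two parts.

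**1. The definition against each airway state**

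| State at onset of bleed | Who can be in it | Blood criterion met? |
|---|---|---|
| Procedural tube in place | LPPSA only, by design | Yes, directly |
| On NCPAP, then intubated | Either arm | Only if blood is then seen in the tube |
| On NCPAP, never intubated | Either arm | No |
| Already ventilated for another reason | Either arm | Yes, directly |

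Only the first row differs by design. The deterioration and X-ray criteria do not depend on arm. Delivery-room intubation is an exclusion in both arms.

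The third row cannot be assumed empty. The section on MV indication does not name pulmonary hemorrhage. Its item on critical circumstances may cover severe cases, but that is left to unblinded care providers.

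**2. How large the first row could make the difference**

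Inputs, all assumed except the 48 h window and the 300 infants per arm:
- *t* = LPPSA tube time divided by 48 h. For 1 h, t = 1/48 = 0.021; for 6 h, t = 6/48 = 0.125.
- *m* = share of true bleeds missed when no tube is in place, the same in both arms.
- Equal true bleed rates, bleeds spread evenly over the 48 h, and every bleed with the procedural tube in place counted.

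Capture in LISA = 1 − m. Capture in LPPSA = t + (1 − t)(1 − m). The apparent LISA/LPPSA ratio is the first divided by the second.

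With m = 1/3:
- 1 h: LPPSA capture = 0.021 + 0.979 × 0.667 = 0.674; ratio = 0.667/0.674 = **0.99**.
- 6 h: LPPSA capture = 0.125 + 0.875 × 0.667 = 0.708; ratio = 0.667/0.708 = **0.94**.

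Varying m:
- m = 0.10: 0.900/0.902 = 0.998 (1 h) and 0.900/0.9125 = 0.99 (6 h).
- m = 0.50: 0.500/0.510 = 0.98 (1 h) and 0.500/0.5625 = 0.89 (6 h).

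In cases, with an assumed true rate of 4% (0.04 × 300 = 12 per arm) and m = 1/3: LISA 12 × 0.667 = 8.0, against LPPSA 12 × 0.674 = 8.1 (1 h) or 12 × 0.708 = 8.5 (6 h). The gap is about half a case or less.

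If every such bleed leads to intubation with blood seen in the tube, m = 0 and the ratio is 1.00. If bleeds cluster around the procedure, the share occurring with the tube in place exceeds t and the ratio falls further below 1.

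**The case against.** The strongest reply is that the LPPSA tube is procedural. LPPSA follows the intubate-treat-extubate model, NCPAP follows in both arms, and later ventilation is governed by the same criteria. For most of the 48 hours the design puts a tube in neither arm. The branch for infants who come to need ventilation lets a bleed on NCPAP count once the infant is intubated and blood is seen in the tube. To be missed altogether, an infant must deteriorate suddenly and have more than two lobes involved, yet never show blood from a tube. The wording also comes from a cited source, and widening it could admit blood from laryngoscopy, which both arms undergo.

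Most of this stands, and it is why the point is minor. It does not remove the point. The ventilation branch satisfies the deterioration criterion, not the blood criterion. The LPPSA tube time has no stated limit. Nothing in the text makes intubation automatic after a bleed.

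A reader might go further and infer that the outcome is materially biased toward LISA. For example, a ratio of 0.67 results if one third of LISA bleeds are missed and no LPPSA bleed is. The documents do not support that. It treats LPPSA infants as if every bleed occurred with a tube in place, whereas after extubation they face the same criterion as LISA infants. Nor does a tube plus raised settings suffice in LPPSA: blood, sudden distress and the X-ray finding are required as well.

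**Conclusion.** The point holds as a minor weakness in the wording of one secondary safety outcome. The definition names a blood source that depends on the device, only LPPSA has that device by design, and the definition's own branch for infants not yet ventilated does not fit it. This permits an under-count in LISA relative to LPPSA; it does not show that one occurs.

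The size cannot be derived from the document. The illustrative ratios of 0.99 to 0.94 rest on assumed tube times, an assumed one-third miss rate common to both arms, and even timing of bleeds. Even timing is the assumption that matters most, and clustering near the procedure would widen the gap. Nothing here affects the primary outcomes or the sample size.

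**What to change.** In the definition, replace the tube as the source of blood with hemorrhagic fluid from the airway, with or without an endotracheal tube. Keep the sudden-deterioration and more-than-two-lobe X-ray criteria unchanged and apply them identically in both arms. Make clear that the one-hour limit runs from the first blood seen at any of these sites. Add one case-report item for whether a tube was in place at onset, so that the dependence on the device can be examined.

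The cost is a one-line change and one data item. Some upper-airway blood from laryngoscopy will have to be classified; the retained deterioration and X-ray criteria limit how much of it can count. Recruitment had already begun, so infants enrolled earlier should be classified from their records under the same wording, by assessors blinded to arm. Where those records do not note blood outside a tube, that should be reported.
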